### Sample Size

The sample size analysis is based on hypothesized change in RMDQ scores. For the primary outcome of change in pain intensity from baseline to week 12, we assume that two-sided α error prob is equal to 0.05 and power is 0.8. The minimal clinically important difference of the RMDQ is prespecified for 3 points (Jordan et al., 2006), and the effect size of RMDQ is in the range of 0.54–0.84 (Saper et al., 2017). We used G-Power Software (version 3.1.9.2, Germany) to estimate the total sample size with the method of *t*-tests-means (difference between two independent means measures in two groups). Considering the effect size of RMDQ is 0.54 and 20% attrition rate, we need a minimum of 138 participants in this study or 69 participants in each group to detect whether 12 weeks of TCQ and grouped-PT have a significant clinical effect on CLBP.

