#### Inclusion and Exclusion Criteria

Target participants will be mainly community-dwelling elderly people who are living in Shanghai. The specific inclusion and exclusion criteria are listed in Table 2. The participants will quit the study if they have been diagnosed with severe diseases (such as heart failure) or serious adverse events occur during the experiment. Besides, the participants will be allowed to voluntarily quit as result of any of their own reasons. We plan to execute the following ways to access our participants as many as possible: (1) Distributing study recruitment flyers in nearby four communities with permission; (2) Sending study recruitment presentations to community healthcare center staff to help introduce potential participants; and (3) Disseminating the recruitment information through electronic communications and anyone interested can contact the recruiter by telephone.

**TABLE 2 T2:** Inclusion criteria and exclusion criteria.

Inclusion criteria	Exclusion criteria
Aged 50–80 years, can speak Chinese and complete the questionnaire survey.	Have practiced tai chi regularly for any reason within the past 6 months or who have practiced tai chi, yoga or qigong for nearly half a year to treat LBP.
Pain, at least 3 months, typically occurs in the area between the lower rib margins and the buttock creases, commonly accompanied by pain in one or both legs.	Have received guided physical therapy for LBP within half a year, including stretching, strength training, motor control training, and so on.
Have had back pain on at least half the time in the last 6 months.	Have specific causes or potential causes of LBP (e.g., sciatica, spinal stenosis, lumbar disk herniation, spondylolisthesis, recent vertebral fracture, and so on).
The average scores of numerical rating scale (in the range of 0–10) ≥3 and ≤8.	Have red flags of serious underlying systemic or visceral disease (e.g., inflammatory disorders malignancy, unexplained weight loss, infections, or recent trauma).
Back-related function scores of Roland-Morris disability questionnaire (in the range of 0–24) ≥5.	Pain in other parts of the body is greater than low back pain.
Have normal cognition or only mild cognitive impairment [the scores of Mini-Mental State Examination (in the range of 0–27) ≥24].	Had prior lumbar spine surgery.
Able to understand the learning process and complete the whole course.	Have history of drug and alcohol abuse.

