#### Roland Morris Disability Questionnaire–Back-Related Function

Roland Morris Disability questionnaire is suitable for evaluating the short-term changes of back-related function after intervention. The questionnaire consists of 24 questions, involving eight facets of walking, standing, bending, lying, dressing, sleeping, self-care, and daily activities (Roland and Morris, 1983). ‘Yes’ (1 point) or ‘No’ (0 point) is answered to each question, and a high total score equates to poor back function. A reduction of 30% on RMDQ score from baseline is identified as minimal clinically important difference for CLBP (Jordan et al., 2006). The RMDQ has an excellent test-retest reliability with an ICC of 0.91 (Brouwer et al., 2004).

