### Data Analysis

Intention-to-treat analysis will be performed regardless of adherence. Microsoft excel 2016 and IBM SPSS Statistics 20.0 (SPSS Inc., Chicago, IL, United States) will be used in data analysis. Continuous variables (e.g., age, body mass index, NRS score, and RMDQ score) will be represented as mean ± standard deviation and be compared using analysis of the independent samples *t*-test. We will use the chi-squared test to analyze the categorical variables (e.g., gender, marital status, smoking, and exercise habits) between the TCQ group and PT group. The baseline demographics characteristics differences between groups will be compared using analysis of *t*-test, variance (ANOVA) or chi-squared tests. If potential confounding factors including gender, age, body mass index, smoking, exercise habits, etc., are present, we will prespecified an adjusted analysis, by using multiple linear regression. At the same time, missing values at week 12, 26, and 52 will be imputed using the multiple imputation.

The co-primary outcomes are the measurement of minimal clinically important difference in NRS and RMDQ scores in two groups after the 12-week intervention, and the paired-sample *t*-test will be carried out for the comparison of the differences. For secondary outcomes, the difference of continuous variables between groups will be compared using the analysis of independent-samples *t*-test. Expenses for LBP or other disease will be explored for cost-benefit analysis. Participants’ global perceived effect, adherence, and health-related quality of life will be compare using appropriate regression. The Fisher exact test will be used to compare adverse events. For the follow-ups phase, two-way repeated-measures analysis of variance (group × time) will be carried out to assess the differences of the primary outcomes (NRS score and RMDQ score) between the two groups. In all analyses, a *P*-value of <0.05 will be considered statistically significant.

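### The RMDQ minimal clinically important difference has two unreconciled definitions, and the paired t-test named for the co-primary outcomes uses neither and does not compare the arms

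*Protocol article*

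**What the plan says.** Three sections of the protocol article bear on this.

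- **Sample Size:** "The minimal clinically important difference of the RMDQ is prespecified for 3 points". The calculation uses a t-test for the "difference between two independent means measures in two groups", and "we assume that two-sided α error prob is equal to 0.05 and power is 0.8". The number itself is reached by "Considering the effect size of RMDQ is 0.54 and 20% attrition rate".
- **Roland Morris Disability Questionnaire (primary outcome):** "A reduction of 30% on RMDQ score from baseline is identified as minimal clinically important difference for CLBP". The reference cited is the one given for the 3 points.
- **Data Analysis:** "The co-primary outcomes are the measurement of minimal clinically important difference in NRS and RMDQ scores in two groups after the 12-week intervention". A paired-sample t-test "will be carried out for the comparison of the differences". The sentence does not say which of the two definitions it means.

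Entry requires "Back-related function scores of Roland-Morris disability questionnaire (in the range of 0–24) ≥5", so eligible baselines run from 5 to 24. The questionnaire has 24 yes/no items, so every score is a whole number.

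Elsewhere the primary outcomes are described as scores: in the abstract, in Study Design and Table 1, in the primary outcome sections, and in the last lines of Data Analysis, where the follow-up analysis is a group-by-time repeated-measures analysis of variance.

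**The concern.** One figure is absolute and the other is relative to baseline, yet both are called the minimal clinically important difference of the RMDQ. Were this only background, the mismatch would be a slip. But Data Analysis writes the term into the definition of the co-primary outcomes, so a reader cannot tell which quantity the trial will report, or whether it is a threshold or a mean.

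The named test does not settle the question. A paired t-test compares two measurements on the same people. It fits before-after change within one arm. It does not fit a yes/no outcome in two separate groups, and it does not estimate the difference between Tai Chi Quan and physical therapy. At stake is whether the headline 12-week analysis answers the comparative question in the title and abstract, and whether a threshold could be chosen once the data are known.

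**Working it through.** **1. The plan's own sample size.** Inputs from Sample Size: d = 0.54, two-sided alpha 0.05, power 0.80, attrition 20%.

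- With n per arm, the two-sample t-test has 2n − 2 degrees of freedom and noncentrality d·√(n/2).
- At n = 55 the noncentrality is 0.54 × √27.5 = 2.83 on 108 degrees of freedom, giving power 0.801. This is the smallest n that reaches 0.80.
- Allowing for attrition: 55 / 0.8 = 68.75, so 69 per arm and 138 in total.

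The stated 138 is reproduced exactly. Neither 3 points nor 30% enters the calculation.

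**2. The two definitions side by side.** The 30% rule needs the smallest whole number that is at least 0.30 × baseline. The other rule always needs 3.

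| Baseline RMDQ | Points needed, 30% rule | Points needed, 3-point rule | 3 points as % of baseline |
|---|---|---|---|
| 5-6 | 2 | 3 | 60-50% |
| 7-10 | 3 | 3 | 43-30% |
| 11-13 | 4 | 3 | 27-23% |
| 14-16 | 5 | 3 | 21-19% |
| 17-20 | 6 | 3 | 18-15% |
| 21-23 | 7 | 3 | 14-13% |
| 24 | 8 | 3 | 12.5% |

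The rules give identical answers at baselines 7-10. A 2-point fall from 5 or 6 meets the 30% rule only. A 3-point fall from 11 or more meets the 3-point rule only.

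**3. How many patients this could touch.** The article gives no baseline mean and no SD of change, so this step rests on assumptions: whole-number scores, baselines restricted to 5-24, and change with mean 3 rounded to whole points.

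| Assumed SD of change | Patients classified differently, over mean baselines of about 9-13 |
|---|---|
| 3 | about 7-17% |
| 4 | about 5-13% |
| 5.5 (about 3 / 0.54 = 5.56, if 3 points were the planned difference) | about 4-10% |

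At SD 4 the 3-point rule gives 55% responders, since P(change ≥ 2.5) = Φ(0.5/4) = 0.55. The 30% rule gives about 43-54% over the same baselines.

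**4. What the paired t-test does under each reading of the co-primary sentence.**

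- *Attainment of the threshold.* The outcome is yes/no in two independent groups. A paired t-test cannot analyse it.
- *Mean change in score.* As normally run, the test asks whether mean change within an arm differs from zero. It uses neither 3 points nor 30% and gives no between-arm estimate. A within-arm test against a fixed shift of 3 points is possible, but the article does not specify one, and it still would not compare arms.

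Sample Size planned on two independent means, so under both readings the test named for the co-primary outcomes differs from the test used for sizing.

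**The case against.** The strongest defence is that no responder analysis is planned. Most sections call the primary outcomes scores, sizing is on means, and no section mentions responders or proportions. The natural reading is then mean change, with the clinical threshold as a benchmark. This largely stands. A reader might infer from Data Analysis that the co-primary endpoint is binary and that its result has two rival answers; the documents support that only as one reading of one sentence.

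A second defence is that 3 points and 30% can coexist, one for groups and one for patients. That is possible, but the article gives both the same name and source and assigns no roles.

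A third is that the paired test suits the first hypothesis in the Introduction, that both treatments have a clinical effect, which Sample Size repeats as its aim. It does suit a within-arm question. It does not suit the comparative objective or the two-group sizing. Nor should one infer that the plan never compares the arms on these scores. The follow-up analysis has a group-by-time term, and the opening of Data Analysis lists NRS and RMDQ scores, alongside age and body mass index, among variables compared by independent-samples t-test. But the sentence devoted to the 12-week co-primary outcomes names only the paired test.

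Three other inferences go too far: that the definitions agree only at a baseline of exactly 10 (in whole points they agree at 7-10); that 138 is wrong because of the conflict; and that the lack of an NRS threshold is an error, since a condensed article may leave it to a plan not shown.

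**Conclusion.** The point holds in a limited form. The article states two definitions of the same threshold without reconciling them, words the co-primary outcomes in terms of that threshold without choosing, and attaches a test that under either reading uses neither definition and does not compare the randomised arms. All of this follows from the text and whole-number arithmetic.

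The discordance of roughly 5-13% is illustrative. It depends on an assumed change of mean 3 and SD 4 and on assumed baselines, widens to about 4-17% when the SD is varied from 3 to 5.5, and matters only if responders are analysed. No effect on a between-arm difference has been shown. The more consequential part is the mismatch between the paired test and a comparative trial sized on two independent means. It should be corrected before analysis.

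**What to change.** - In Data Analysis, define the co-primary outcomes as NRS and RMDQ scores at week 12 (or change from baseline). Analyse them as between-arm mean differences adjusted for baseline. Keep within-arm change as descriptive support.
- State one RMDQ threshold for patient-level response, for example the 30% reduction already in the outcome section. Use it only for a secondary responder outcome, compared between arms as a proportion (risk difference or logistic regression).
- Describe 3 points as a group-level benchmark for interpretation. Do not present it as the basis of 138, which follows from d = 0.54, nor as a non-inferiority margin, since none is stated.

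**Cost.** The definitions need wording only. Moving the co-primary analysis to a between-arm difference is more than wording: the first hypothesis in the Introduction and the closing aim in Sample Size, both framed as an effect of each treatment, must be brought into line. This change requires no new sample size, because the calculation already assumes two independent means. A responder outcome promoted to primary would require one, from response rates the article does not give. Allocation by community is a separate matter that this change does not address.

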### Participants

#### Randomization and Blinding

We will take a community randomized approach, and four communities will be assigned with an allocation of 1:1 through the random numbers generated by the analyst. Finally, two communities will be assigned to the TCQG, and two to the PTG. We will recruit participants in the corresponding community to practice TCQ or PT. Throughout the courses of the trial, all study assessors who are responsible for collecting outcomes will be blinded to the hypotheses and allocation. Meanwhile, we shall maintain separation between the assessors and assistants who are responsible for recruitment work and between the assessors and class instructors. In addition, participants should conceal their group status to the assessors. Participants have informed consent and are blinded impossibly without a placebo. Finally, all data analyst do not know group allocation and deal with coded data instead of the names of the participants.

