**Methods:**

We will perform a single-blind randomized controlled trial on elderly people with chronic low back pain. 138 participants will be randomly assigned to the Tai Chi Quan group (60-min classes, three times per week for 12 weeks) or physical therapy group (10 min of evaluation and warm-up, 40 min of therapist-directed exercise therapy, and 10 min of relaxation, three times per week for 12 weeks) with an allocation of 1:1. The participants will be followed up for 40 weeks for the study of long-term effects. The primary outcomes include pain intensity and back-related function at 12 weeks. Secondary outcomes include lumbar quantitative sensory testing, balance, cognitive function, psychosocial function, cost-effectiveness, compliance and adverse events. We will perform the intention-to-treat analysis for withdrawal and missing data.

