## Study Design and Methods

### Study Design

The study is a single-blinded RCT of TCQ classes or grouped-PT for patients with CLBP (Figure 1. Study flow diagram). Eligible participants will be randomly assigned into the Tai Chi Quan group (TCQG) or physical therapy group (PTG). Both groups will perform exercises for 60 min three times a week for a total of 12 weeks. After the program, 40 weeks of follow-ups will be conducted.

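### Four communities are randomised, two per arm, but the sample size and the named between-group tests treat participants as independent, so 80% power is not supported

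*Protocol article*

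**What the plan says.** The protocol article describes two different units of randomisation.

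- Participants: the abstract's Methods paragraph says "138 participants will be randomly assigned to the Tai Chi Quan group" or to physical therapy, and Study Design begins "Eligible participants will be randomly assigned into the Tai Chi Quan group (TCQG) or physical therapy group (PTG").
- Communities: Randomization and Blinding says "We will take a community randomized approach, and four communities will be assigned with an allocation of 1:1" and "two communities will be assigned to the TCQG, and two to the PTG". It continues: "We will recruit participants in the corresponding community to practice TCQ or PT". A participant's arm is therefore the arm of the community.

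The Sample Size section uses the G-Power t-test for a "difference between two independent means measures in two groups", with two-sided alpha 0.05, power 0.8, effect size 0.54 and 20% attrition. This gives 69 per group, 138 in total. No ICC, design effect or number of communities enters.

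For secondary outcomes, Data Analysis says "the difference of continuous variables between groups will be compared using the analysis of independent-samples" t-tests. It also names chi-squared and Fisher tests, multiple linear regression on participant characteristics, and a group-by-time repeated-measures ANOVA for the primary outcomes in follow-up, all at the 0.05 level. Community is not named as a term in any of them. For the week-12 co-primary outcomes it names a paired t-test.

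**The concern.** When whole communities are allocated, people in one community tend to resemble each other, and the arm comparison rests on the number of communities as well as the number of people. A test that counts 110 independent completers then understates the standard error: it rejects too often under the null, and the quoted power belongs to a different design. With two communities per arm, a valid comparison also has very few degrees of freedom. At stake is whether the between-group results can carry the weight that the Discussion gives them in judging tai chi as an alternative to physical therapy.

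**Working it through.** **Inputs.** From the Sample Size section: d = 0.54, two-sided alpha 0.05, power 0.80, attrition 20%. From Randomization and Blinding: 2 communities per arm. Assumed, because the protocol does not give it: ICC of 0.01, 0.02, 0.05 or 0.10, with 0 as reference, and equal community sizes.

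**Step 1: reproduce the 138.** The exact two-sample t-test (noncentral t) gives power 0.794 at 54 per arm and 0.801 at 55, so 55 are needed. Then 55 / (1 − 0.20) = 68.75, rounded up to 69 per arm, or 138. The stated figure is correct for independent participants, that is, for a design effect of 1.

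**Step 2: design effect.** With 55 analysed per arm in 2 communities, m = 55 / 2 = 27.5, and DE = 1 + (m − 1) × ICC = 1 + 26.5 × ICC. At ICC 0.05, for example, DE = 1 + 1.325 = 2.325.

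**Step 3: type I error of an unadjusted independent t-test.** The true variance of the arm difference is DE times what the test assumes, so the error is about 2 × [1 − Φ(1.96 / √DE)]. At ICC 0.05: 1.96 / 1.525 = 1.285, giving 0.199. Simulation with communities of 28 and 27 (200,000 runs) gave 0.081, 0.113, 0.203 and 0.316 for the four ICC values, and 0.050 at ICC 0.

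**Step 4: power of a valid community-level t-test.** Each arm mean averages 2 communities, so the standardised difference has variance 2 × DE / (2m) = DE / 27.5. The noncentrality is 0.54 × √(27.5 / DE) = 2.832 / √DE. Degrees of freedom are 4 − 2 = 2, and the two-sided critical value is 4.303.

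| ICC (assumed) | DE | 110 / DE | Type I error, unadjusted t-test | Noncentrality | Power, 2 df |
|---|---|---|---|---|---|
| 0 | 1.00 | 110 | 5% | 2.83 | 36% |
| 0.01 | 1.27 | 87 | 8% | 2.52 | 30% |
| 0.02 | 1.53 | 72 | 11% | 2.29 | 26% |
| 0.05 | 2.33 | 47 | 20% | 1.86 | 20% |
| 0.10 | 3.65 | 30 | about 31% | 1.48 | 15% |

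**Step 5: can more participants in the same four communities repair it?** As m grows without limit, DE / m tends to the ICC and the noncentrality to 0.54 / √ICC. The 2-df test then reaches at most 77%, 53%, 29% and 18% for the four ICC values. At 27.5 analysed per community, at least 80% power needs 4, 5, 6 and 9 communities per arm.

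**The case against.** - *The loss depends on a figure the protocol does not give.* This stands. At an ICC of exactly 0 the unadjusted t-test keeps 5% and 80%, so a reader should not infer that 0.05 is proven to fail. But nothing in the protocol supports an ICC of 0, and exercise in shared classes and in therapist-led groups makes independence less plausible.
- *The error figures do not describe every test.* This also stands. The co-primary sentence names a paired t-test, which compares within a group, and the regression for global perceived effect, adherence and quality of life is unspecified. The figures apply to the independent t-test, which Data Analysis names for secondary outcomes and for continuous variables generally, with NRS and RMDQ among its examples. The group-by-time ANOVA, a between-group test of the primary outcomes, shares the independence assumption.
- *Arm and community are fully confounded.* A reader might infer this, but it goes too far. Two communities are nested in each arm, so variation between communities can be estimated, although with only 2 df. Full confounding would need one community per arm.
- *No two-sided p-value can fall below 0.33.* That floor (2 of 6 possible allocations) belongs to a permutation test, which the protocol does not plan. It limits one alternative analysis and is not an error in a stated figure.
- *An unseen analysis plan may adjust for community.* It may, which would address the error rate. It cannot make four communities deliver 80% power over the assumed range (Step 5).
- *Cluster allocation is a legitimate choice.* Agreed. The fault is the conflict over the unit of randomisation and a sample size that fits only one of the two designs.

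**Conclusion.** The concern holds in this form. The protocol contradicts itself on whether participants or communities are randomised. Its sample size and named between-group tests fit only independent participants, while its randomisation section allocates four communities. The arithmetic of 138 is right; its premise does not match that section. If communities are the unit, a valid comparison has about 30% to 15% power instead of 80%, and an unadjusted independent t-test has a type I error of about 8% to 31%. Both ranges rest on an assumed ICC of 0.01 to 0.10, 55 analysed per arm and equal community sizes. The 36% at ICC 0 needs no assumption of clustering: it reflects the 2 df alone. If participants are in fact the unit, the 138 stands, apart from clustering by class or therapist.

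**What to change.** Reconcile the abstract, Study Design and Randomization and Blinding so that they state one unit of randomisation.

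**If communities are the unit:**
- Call the trial cluster-randomised.
- Withdraw the 80% statement and give power from the 2-df analysis over a stated ICC range. Do not substitute power computed only from the reduced effective sample size (about 70% down to 30% over the same ICC range), because the 2-df analysis does not deliver it.
- Make between-group comparisons at community level, or with a mixed model that has a community effect and small-sample (2 df) inference.
- Report the arm difference mainly as an estimate with its interval.

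This costs an amendment, a changed analysis model and a much more modest power claim, with no extra participants. Keeping 80% with community allocation would instead need the larger numbers of communities in Step 5, and more participants with them.

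**If allocation has not been drawn and both programmes can be offered in every community:** randomise individuals 1:1, stratified by community. The abstract and Study Design already describe individual assignment; the stratification would be new. N = 138 is kept. The costs are contamination between neighbours and delivery of both programmes, with their coaches and therapists, in all four communities. Clustering by class or therapist would remain and should be allowed for.

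### As the randomisation section is written, each community's arm is fixed before its participants are recruited, so entry can depend on the treatment offered; the abstract and Study Design describe a different order

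*Protocol article*

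**What the plan says.** The Randomization and Blinding section of the protocol article makes the community the unit of allocation, with four communities allocated 1:1 by random numbers that an analyst draws. The result is stated as follows: "Finally, two communities will be assigned to the TCQG, and two to the PTG". The next sentence turns to recruitment: "We will recruit participants in the corresponding community to practice TCQ or PT".

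On blinding, the same section says that "all study assessors who are responsible for collecting outcomes will be blinded to the hypotheses and allocation", and that "we shall maintain separation between the assessors and assistants who are responsible for recruitment work and between the assessors and class instructors". Participants cannot be blinded. Data analysts are blinded ("all data analyst do not know group allocation and deal with coded data"). Recruitment staff are not listed among those blinded.

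Two other places describe allocation differently. The Methods part of the abstract says that the 138 participants are assigned at random, and the Study Design section says that eligible participants are. Both read as allocation of individuals, and the second places it after eligibility.

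The Inclusion and Exclusion Criteria section recruits through flyers in the four communities, introductions by community health staff, and electronic notices with contact by telephone. The Data Analysis section plans intention-to-treat, multiple imputation and, if confounding factors are present, regression on factors such as gender, age, body mass index, smoking and exercise habits.

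**The concern.** Random allocation protects a comparison when it cannot influence who enters each arm. If communities are allocated first and people are then enrolled for a named treatment, that protection is lost at the participant level. People who like Tai Chi may come forward in two communities, and people who want therapist-led care in the other two. A recruiter who knows the arm may also apply the judgement items in Table 2 differently, for example whether someone can complete the course or has another condition that might confound the treatment effect.

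The co-primary outcomes are pain and function as reported by unblinded participants. Differences in expectation, motivation or prognosis therefore act on exactly what is measured, and blinded assessors give little protection. Such a bias could create a difference or hide a real one, and the second possibility bears on the stated non-inferiority hypothesis. It does not shrink as the sample grows, and it cannot be repaired after enrolment.

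**Working it through.** **1. Order of steps.** The three statements, side by side:

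| Place in the article | Who is allocated | When |
|---|---|---|
| Abstract, Methods | Participants | Not stated |
| Study Design | Eligible participants | After eligibility |
| Randomization and Blinding | Four communities | Before recruitment in each community |

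The third is the dedicated and most specific account. Recruiting in the community that corresponds to a treatment makes sense only once that community's arm is set. Under the first two accounts, with individual and concealed allocation, the recruitment concern would fall away.

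**2. Who can know the arm.** Volunteers can, because they are recruited to practise one named treatment. For recruiters it is an inference from three points: they enrol people for that treatment, they are left out of the blinding statement, and they are kept apart from the blinded assessors just as the class instructors are.

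**3. Whether the plan contains a repair.**
- Intention-to-treat keeps the groups as recruited, including any selection.
- The adjusted analysis is conditional and names measured factors. Treatment preference and expectation are not among them.
- Allocating 4 communities two and two allows C(4,2) = 6 allocations. That is too few to balance participants, and it does not govern who enrols afterwards.

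**4. The plan's own sample size.** The inputs in the Sample Size section are effect size 0.54, two-sided alpha 0.05, power 0.80 and 20% attrition. The two-sample t-test calculation gives 54.8, rounded up to 55 per arm. Then 55 / (1 − 0.20) = 68.75, rounded up to 69 per arm, or 138 in total. The stated figure reproduces, but it offers no protection against this bias.

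**5. Illustration of size.** These assumptions are not in the article:
- SD = 3 / 0.54 = 5.56 RMDQ points. This pairs the 3-point minimal important difference with the effect size of 0.54. The article gives both but does not link them.
- 55 analysed per arm, no true treatment effect, and an independent-samples t-test at two-sided 0.05 (108 degrees of freedom, critical value 1.982).
- Selection alone shifts one arm's mean RMDQ by s points. The standardised shift is d = s / 5.56, and the noncentrality is d × √(55/2).

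| Shift s (points) | d | Noncentrality | Probability of p < 0.05 |
|---|---|---|---|
| 0.5 | 0.09 | 0.47 | 7.5% |
| 1 | 0.18 | 0.94 | 15.5% |
| 2 | 0.36 | 1.89 | 46.5% |

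At the other end of the stated effect-size range, SD = 3 / 0.84 = 3.57, and shifts of 1 and 2 points give 31% and 83%.

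**The case against.** Several objections have weight.

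- **Recruiters' knowledge is not stated.** A reader might infer that recruiters, community health staff and volunteers all certainly know the arm before consent. The article does not say so. The recruitment section describes a single campaign across the four communities and mentions no arm-specific flyer. Separating assessors from recruiters protects the assessors' blinding and does not say what recruiters know. This stands. For recruiters the inference is strong but remains an inference, and for health staff the text is silent.
- **Other sections describe participant-level allocation, and an article condenses.** The flow diagram is not available, and concealment details may be in a fuller protocol. It would be too strong to say that the trial has no allocation concealment at participant level. But the point does not rest on silence: the order of steps is written in the randomisation section and conflicts with the Study Design section.
- **Partial safeguards exist.** Table 2 excludes recent regular Tai Chi and recent guided physical therapy, and it bounds pain (NRS 3 to 8) and function (RMDQ at least 5). Communities are still allocated at random, so it would be wrong to say that randomisation does nothing. These features reduce the risk but do not control expectation or motivation.
- **The size is hypothetical.** The shifts have no source in the article. The planning text refers to change from baseline, and the Data Analysis section names a paired test for the co-primary outcomes, so the modelled test may not be the one used. Hence the figures illustrate and do not estimate.
- **The analyst.** Allocation comes "through the random numbers generated by the analyst", while data analysts are said not to know it. A reader might infer that one person does both, which would break the blinding. The text does not show that, so this is a minor point of wording.

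**Conclusion.** The point holds in limited form. The article contradicts itself on who is allocated and when. If the randomisation section is followed as written, participants are recruited after their community's arm is fixed, and preference or prognosis can then differ between arms in a way that the planned analysis cannot remove.

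The amount of bias cannot be known from the document. Under the stated assumptions, a shift of half a point raises the false-positive rate only from 5% to about 7.5%. A shift of 1 point, one third of the 3-point important difference, raises it to about 15%, and 2 points to about 46%.

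The conclusion depends on the randomisation section describing what is really done. If individuals are randomised after eligibility with concealed allocation, what remains is the contradiction in the text.

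**What to change.** 1. Reconcile the abstract, the Study Design section and the Randomization and Blinding section. State one unit of allocation and one order for recruitment, screening, consent, baseline and disclosure of the arm.
2. If communities remain the unit, complete recruitment, screening, consent and baseline in all four, with the same neutral material, before allocation is drawn or disclosed.
3. If individuals are randomised, disclose each allocation only after that participant's baseline assessment.
4. As a small clarification, state that the person who draws the allocation is not the blinded data analyst.

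The change is mainly one of sequence. Its costs are a later class start in the communities that finish recruiting first, and possibly some dropout between consent and the first class.
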